## Methods

### Reform to the general medical services contract in England

The 2014/15 General Medical Services contract introduced a requirement for
general practices in England to offer patients aged 75 or over a named
accountable general practitioner, who should provide longitudinal continuity of
care within the general practice and be accountable for coordinating care to
meet the patient’s health and social care needs. In particular, the named
accountable general practitioner should ensure that patients receive all
appropriate services and work with relevant associated healthcare and social
care professionals to deliver a multidisciplinary care package [24,35]. The contract requires that the practice notify the patient of their
named accountable general practitioner, usually by letter, and make a reasonable
effort to accommodate patient preferences about the choice of general
practitioner. However, patients are not prevented from seeing any other general
practitioner in the practice [36]. The
2014/15 GMS contract changes led to a step change (discontinuity) in the
percentage of patients receiving a named accountable general practitioner, which
increases from around 5% to around 80% near age 75 (Table 1).

**Table 1 T1:** Preliminary analysis of data from Clinical Practice Research Datalink
showing that the requisite discontinuity exists in the data.

	Patients aged 70–74 (%)	Patients aged 75–79(%)

Notified of named accountable general practitioner	5420 (5%)	67,770 (80%)
Not notified of named accountable general practitioner	99,830 (95%)	17,161 (20%)
Total	105,250	84,931

*Note:* Based on preliminary analysis of Clinical
Practice Research Datalink data. Figures are illustrative as this
analysis was based on 2014 data and not all exclusion criteria were
applied.

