### Exposure variable and index dates

For reasons of patient confidentiality, Clinical Practice Research Datalink
contains year of birth rather than full date of birth. Therefore, age will be
calculated by subtracting the year of birth from 2014, and we will compare
patients whose age was in a small bandwidth (interval) above and below 75 years.
This bandwidth will be selected using standard cross-validation methods [31].

We will report the proportion of patients in each age group who received the
intended treatments. Since the policy ensures that the vast majority of patients
who are eligible for a named accountable general practitioner within 2014/15
will have received one by September 2014, treatment receipt will be based on the
presence of a recorded named accountable general practitioner within a 6-month
period (April 2014 to September 2014), using the Read code prescribed by the
General Medical Services contract (67DJ). Patients without a recorded named
accountable general practitioner by September 2014 will be regarded as untreated
patients, even if they received a named accountable general practitioner
subsequently.

All patients will be assigned an index date for the purposes of calculating
endpoints and covariates. For patients who are assigned a named accountable
general practitioner between April and September 2014, this will be the date at
which this was recorded. Patients who are not assigned a named accountable
general practitioner during this period will be randomly assigned an index date,
such that the distribution of index dates across months is the same as for those
patients who did receive one. Thus, all patients will have at least 6 months
follow-up within 2014/15, before the policy was extended to all patients
irrespective of age [39].

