### Study endpoints and covariates

Our primary endpoint will be the number of general practitioner contacts per head
over 6 months; this will include all appointment types (e.g. both surgery visits
and telephone calls). Secondary endpoints, also calculated over 6 months, will
be a measure of longitudinal continuity of care; the number of contacts with
general practitioners or practice nurses; numbers of referrals to specialist
care; and number of common diagnostic tests (e.g. blood pressure). There are
several measures of longitudinal continuity of care, which focus on the
concentration, dispersion, distribution or sequence of consultations [12,17]. The Usual Provider of Care index measures the proportion of
contacts with the general practitioner who is most commonly seen [17]. The Usual Provider of Care index is
widely used [11] and is more easily
interpreted than some of the other measures [12]. The Usual Provider of Care index was not chosen as the primary
endpoint, as this measure is only defined for the subgroup of study participants
with at least two general practitioner contacts during the study period. The
theory behind the intervention is such that a change to the number of general
practitioner contacts, referrals to specialist care or numbers of diagnostic
tests is more likely following an improvement to continuity of care. However, we
will analyse these endpoints regardless of the findings for the Usual Provider
of Care index, since it is theoretically possible that, for example, the letters
led to an increase in enquiries from patients without improvements to
continuity.

The following covariates will be calculated for all patients, using data recorded
prior to the index date: gender; ethnicity; socioeconomic score (attributed to
the patient according to their area of residence, and measured by deciles of the
Index of Multiple Deprivation 2010) [40];
number of long-term health conditions recorded prior to the index date; and
numbers of general practice contacts, referrals to specialist care, diagnostic
tests and hospital discharges in the 6 months prior to the index date. Long-term
conditions will be defined in accordance with the Quality and Out-comes
Framework. The data quality for the Quality and Outcomes Framework indicators is
enhanced as a result of these conditions forming part of the pay-for-performance
scheme for general practice [41].

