## Statistical methods

Our initial analysis (Table 1) suggests that
the proportion of patients receiving a named accountable general practitioner is
discontinuous at the threshold, but this will be confirmed on receipt of the data.
We will also confirm that, although we would expect a trend in certain covariates
across age, there are no discontinuities in these covariates at age 75. This
comparison will be done graphically and include all patients, regardless of actual
treatment assignment. We do not expect such discontinuities to occur, but if they do
exist, this would lead us to question the validity of our study design.

As mentioned previously, the proportion of patients receiving a named accountable
general practitioner is unlikely to jump from 0 to 100% at age 75. It will therefore
be appropriate to apply a fuzzy regression discontinuity design [31], by fitting four regression models. Two
models will relate the outcome to a polynomial function of age: one model will be
fitted for people whose age lies within the bandwidth below the threshold and the
other model for people within the bandwidth above the threshold. The final two
models have treatment assignment as their dependent variable rather than outcome.
All models will use ordinary least squares regression and include patients
irrespective of their actual treatment assignment. We will calculate the estimated
treatment effect as the difference between the predictions of the two outcome models
at age 75, divided by the difference between the predictions of the two treatment
models at age 75.

The analysis will have regard to the rounded nature of the running variable (i.e.
age), resulting from the use of year of birth rather than full date of birth. This
will exclude the use of very small bandwidths, and so we will use a larger interval
spanning several years and model any trend in the endpoints by age using parametric
approaches based on polynomial functions [42,43]. In the absence of
information on full date of birth, it will not be possible to establish for a given
patient born in 1939 what date they turned 75, and therefore which side of the
threshold the patient is at the index date. We will remove the risk of
misclassification by excluding all patients born in 1939 when fitting the regression
models and making a small extrapolation around age 75 [42]. A final consideration is that, when the running variable
is only observed at discrete points, discretisation bias can occur because a change

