in slope close to the cut-off might be mistaken for a treatment effect when in fact
it is due to the ‘natural’ change in outcomes with age. We will correct
for this bias using a method that is based on the moments of the age distribution
[42].

We will conduct a series of additional specification tests to check the validity of
the study design [31]. First, we will repeat
the estimation procedure at non-discontinuity points, to confirm a treatment effect
of zero. Second, we will confirm that the estimated treatment effect is not
sensitive to the choice of bandwidth or order of polynomial. Third, we will repeat
the analysis when including covariates in the regression models. Although it is not
necessary to include covariates in regression discontinuity analyses, including them
may improve precision [37,42].

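### The utilisation baseline is counted back from an index date inside the policy period, so the age-75 check on prior contacts, referrals, tests and discharges is not a clean pre-policy check

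*Protocol article*

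**What the plan says.** All references are to the protocol article.

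- **Start of eligibility** (Reform to the general medical services contract in England): "The 2014/15 General Medical Services contract introduced a requirement for" practices to offer a named GP to patients aged 75 or over. Notification is usually by letter.
- **Index date** (Exposure variable and index dates): receipt is judged over a 6-month "period (April 2014 to September 2014"). A treated patient's index date is the day the named GP was recorded. An untreated patient gets a random date, "such that the distribution of index dates across months is the same as for those" who were treated.
- **Baseline** (Study endpoints and covariates): utilisation covariates are practice contacts, referrals, "tests and hospital discharges in the 6 months prior to the index date". The long-term condition count is also cut at the index date. Gender, ethnicity and area deprivation (IMD 2010) are on the same list.
- **Use of the covariates** (Statistical methods): the authors will confirm graphically, in all patients, that "there are no discontinuities in these covariates at age 75", and say that a failure would make them doubt the design. The third specification test adds covariates to the regressions.
- **Other falsification test** (Statistical methods): the authors will repeat "the estimation procedure at non-discontinuity points, to confirm a treatment effect" of zero. This is done away from age 75.

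**The concern.** In a fuzzy regression discontinuity design the instrument is age eligibility. A covariate used to test smoothness at the threshold should therefore be fixed before eligibility starts, and not merely before recorded receipt. Those born in 1939 are left out of the models, so every fitted patient above the threshold was already 75 when the contract began. For these patients any look-back beyond the start of April 2014 is time spent under the policy.

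Prior utilisation is the covariate closest to the primary endpoint, so it carries most of the weight in the validity check. If it jumps at 75, there are three candidate explanations, and the planned check cannot separate them:

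1. The policy acted before the code was entered.
2. The look-back is anchored differently in treated and untreated patients.
3. Contacts already jumped at 75 before the reform.

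Only the third threatens the design. The placebo cut-offs at other ages say nothing about it. In the adjusted analysis, a baseline that already contains policy effect would absorb part of the effect being estimated.

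**Working it through.** The protocol prints no figure for the overlap, so there is none to reproduce.

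**Inputs.** Index dates run from 1 April to 30 September 2014, with a look-back of 6 calendar months. Eligibility is taken to start on 1 April 2014. This is an assumption: the exact day is not printed, but the receipt window opens that month.

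**Overlap formula.** Share after eligibility = days from 1 April 2014 to the index date ÷ days in the 6-month look-back.

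- Index 30 June: 90/182 = 49%.
- Index 1 July: 91/181 = 50.3%. Every later index date is above one half.
- Index 30 September: 182/184 = 99%.

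| Index month | Mean share after 1 April |
|---|---|
| April | 8% |
| May | 25% |
| June | 41% |
| July | 59% |
| August | 76% |
| September | 91% |

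**Average over patients.** The monthly distribution of index dates is not given, so three are assumed.

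- Even spread: 50%.
- Front-loaded (40/25/15/10/6/4% from April to September): 0.40×8 + 0.25×25 + 0.15×41 + 0.10×59 + 0.06×76 + 0.04×91 ≈ 30%.
- Back-loaded (the reverse): ≈ 70%.
- Look-back ending 31 March 2014: 0% for everyone.

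**Anchoring.** From Table 1 (illustrative 2014 data), the share with a recorded named GP, and hence an event-based index date, is 5,420/105,250 = 5% at ages 70–74 and 67,770/84,931 = 80% at ages 75–79. If coding tends to follow a contact, event-anchored look-backs would hold more contacts than randomly anchored ones, and the mean would step up at 75 without any policy effect.

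**Effect on the adjusted analysis.** Effect removed ≈ slope of outcome on baseline × policy effect contained in the baseline. The document gives neither factor. As an illustration, take the target effect of 5% × 5 = 0.25 contacts and a slope of 0.4 to 0.7 (assumed).

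- Nothing precedes coding: 0 removed, 0%.
- Full effect present for a quarter of the look-back (assumed): 0.25 × 0.25 = 0.0625 contacts in the baseline. The amount removed is 0.4 × 0.0625 = 0.025 to 0.7 × 0.0625 = 0.044, or 10% to 18% of 0.25.

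The illustrated range is therefore 0% to 18%, driven by a lag that the document does not state.

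**The case against.** Overlap with the policy calendar is not contamination by treatment. Each treated patient's look-back stops at recorded receipt, and patients counted as untreated have no record by September 2014. Index months are matched between treated and untreated, so the overlap does not by itself create a step at 75. Something must act before coding, and no section states a lag between letter and code. This stands, and it is why the bias cannot be sized. The mechanism is still plausible on the protocol's own account: it allows that letters may prompt enquiries, and it does not say that coding comes before or with the letter. The anchoring difference needs no lag.

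A reader might also infer three stronger things that the document does not support.

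- **That the plan is blind to a pre-existing jump at 75.** A persistent jump would usually show in the planned check whatever the calendar window, unless an opposite policy effect masked it. The likelier failure is a false alarm or an unreadable result.
- **That no check at 75 is pre-policy.** Gender, ethnicity and IMD 2010 cannot be moved by the reform. The point is limited to utilisation and, less strongly, the long-term condition count.
- **That the main result is biased by this baseline.** The four main regressions use age alone. Covariates enter only in a specification test, described as optional and for precision.

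Finally, a pre-policy placebo at 75 may appear in a fuller plan not shown, so its absence from the article is not itself an error. The look-back rule, however, is stated text.

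**Conclusion.** The point holds for the utilisation covariates. Their baseline lies partly after age eligibility began: 8% on average for April index dates, 91% for September, and at most 99%. The overall mean is about 50% if index dates are evenly spread and 30% to 70% under the other spreads tried, taking eligibility to start on 1 April 2014.

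The consequence is ambiguity. A step at 75 in prior contacts, referrals, tests or discharges would have at least three readings, and the authors say that a step would make them doubt the design. Any loss of effect in the adjusted analysis cannot be quantified from the document and may be zero. Severity is minor: one validity check and one sensitivity analysis are affected.

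**What to change.** 1. Count contacts, referrals, tests and hospital discharges for every patient in one fixed window, 1 October 2013 to 31 March 2014, and take long-term conditions as of 31 March 2014.
2. Use these values in both the continuity check at 75 and the covariate-adjusted models.
3. Estimate the jump at 75 in GP contacts, referrals and tests within that window, using the same models, bandwidth and 1939 exclusion, and report it with a 95% confidence interval.

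This removes the policy period and the mix of event-based and random anchors from the baseline. It also gives a direct test of the main outcome at the real threshold before the reform.

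The cost is a change of wording and one extra run. Records back to October 2013 are already needed for patients indexed at the start of April 2014. The downside is a baseline up to 6 months older for late index dates, and so slightly less prognostic.

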## Statistical methods

Our initial analysis (Table 1) suggests that
the proportion of patients receiving a named accountable general practitioner is
discontinuous at the threshold, but this will be confirmed on receipt of the data.
We will also confirm that, although we would expect a trend in certain covariates
across age, there are no discontinuities in these covariates at age 75. This
comparison will be done graphically and include all patients, regardless of actual
treatment assignment. We do not expect such discontinuities to occur, but if they do
exist, this would lead us to question the validity of our study design.

As mentioned previously, the proportion of patients receiving a named accountable
general practitioner is unlikely to jump from 0 to 100% at age 75. It will therefore
be appropriate to apply a fuzzy regression discontinuity design [31], by fitting four regression models. Two
models will relate the outcome to a polynomial function of age: one model will be
fitted for people whose age lies within the bandwidth below the threshold and the
other model for people within the bandwidth above the threshold. The final two
models have treatment assignment as their dependent variable rather than outcome.
All models will use ordinary least squares regression and include patients
irrespective of their actual treatment assignment. We will calculate the estimated
treatment effect as the difference between the predictions of the two outcome models
at age 75, divided by the difference between the predictions of the two treatment
models at age 75.

The analysis will have regard to the rounded nature of the running variable (i.e.
age), resulting from the use of year of birth rather than full date of birth. This
will exclude the use of very small bandwidths, and so we will use a larger interval
spanning several years and model any trend in the endpoints by age using parametric
approaches based on polynomial functions [42,43]. In the absence of
information on full date of birth, it will not be possible to establish for a given
patient born in 1939 what date they turned 75, and therefore which side of the
threshold the patient is at the index date. We will remove the risk of
misclassification by excluding all patients born in 1939 when fitting the regression
models and making a small extrapolation around age 75 [42]. A final consideration is that, when the running variable
is only observed at discrete points, discretisation bias can occur because a change
in slope close to the cut-off might be mistaken for a treatment effect when in fact
it is due to the ‘natural’ change in outcomes with age. We will correct
for this bias using a method that is based on the moments of the age distribution
[42].

We will conduct a series of additional specification tests to check the validity of
the study design [31]. First, we will repeat
the estimation procedure at non-discontinuity points, to confirm a treatment effect
of zero. Second, we will confirm that the estimated treatment effect is not
sensitive to the choice of bandwidth or order of polynomial. Third, we will repeat
the analysis when including covariates in the regression models. Although it is not
necessary to include covariates in regression discontinuity analyses, including them
may improve precision [37,42].

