### Required sample size

We believe that a 5% change in the number of general practice contacts would
represent a meaningful difference to general practice workload, since this
represents approximately one extra appointment per working day for an average
general practitioner [46]. Assuming an
average of 5 general practitioner contacts per 6-month period in the absence of
a named accountable general practitioner [47], and a standard deviation of 6 contacts [47,48], we will need
24,212 patients in each treatment group, at 90% power and two-sided p-value of

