### Strengths and limitations

Four characteristics of this study distinguish it from existing work in this
area. First, this study will examine a national policy intervention to integrate
care, as opposed to particular local initiatives to encourage more integrated
services. The nature of national initiatives means that the prescribed
intervention might not suit all local contexts and there may be limited local
buy-in to change, potentially limiting effectiveness. However, contracts are a
potentially important method of encouraging more continuity of care, and we are
not aware of previous studies that have investigated the effectiveness of such
an approach.

Second, previous studies have examined integrated care within pilot areas [21], but the current study will use a large
database to examine a national sample of general practices, increasing the
generalisability of its results. The Clinical Practice Research Datalink
database is broadly representative of the UK population [41], though our sample will be limited to those that have
consented to participate in the Clinical Practice Research Datalink linkage
scheme and in addition have submitted data to Clinical Practice Research
Datalink in a timely fashion. While it will not be possible for us to document
the intervention as closely as pilot studies, we will investigate whether the
effectiveness of the policy varies according to local characteristics. If some
areas perform better than others, then future studies could use qualitative
methods to construct theories for why these areas saw more promising results
[50]. The current study is an example
of a relatively new approach that applies surveillance methods to national
databases to identify areas of good practice, rather than starting with
prospective studies of a small number of selected pilots, which may not show the
anticipated returns [51].

Third, the large sample size means that we will have statistical power to detect
small effects, such as a 5% change in the number of general practitioner
contacts. This is important because many previous studies of out-of-hospital
interventions have assumed relatively large effect sizes when estimating the
required sample size, for example that emergency hospital admissions could be
reduced by 15% within 12 months [52,53]. Where such studies fail to detect
changes, it is unclear whether this is due to an ineffective intervention or
simply that the study was underpowered to detect small yet meaningful effects.

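### The rounded age is handled only in the point estimate: no stated interval allows for birth-year misfit, and power is argued from patient counts although at most 10 ages per side carry the trend

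*Protocol article*

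**What the plan says.** Under Exposure variable and index dates, "age will be calculated by subtracting the year of birth from 2014". Study cohorts limits births to 1929–1949. Statistical methods reaches age 75 by "excluding all patients born in 1939 when fitting the regression models and making a small extrapolation around age 75". Outcome and treatment receipt are each modelled by separate polynomials below and above the threshold, and the effect is the ratio of the two jumps. On fitting, the article says "All models will use ordinary least squares regression and include patients irrespective of their actual treatment assignment".

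The article recognises that age is rounded. Its stated responses are:

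- a wider bandwidth;
- parametric polynomials;
- removal of the 1939 births;
- a moments-based correction of discretisation bias;
- repeat estimation at points where no jump is expected;
- variation of bandwidth and polynomial order;
- a repeat analysis with covariates.

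Strengths and limitations admits that the estimates depend on model specification.

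On precision, Required sample size asks for "24,212 patients in each treatment group, at 90% power and two-sided p-value of" 0.05. It adds that exact power depends on the bandwidth and that the database holds more than enough patients. Strengths and limitations then says that "the large sample size means that we will have statistical power to detect small effects", with a 5% change in contacts as the example.

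**The concern.** Everyone born in the same year has the same age value, and so shares any gap between that year's true mean and the fitted polynomial. More patients per year do not average this gap away. The jump at 75 is extrapolated from 5 to 10 birth-year means per side, so such gaps pass straight into it.

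The listed remedies do not say how this uncertainty reaches the confidence interval. With about 17,000 to 21,000 patients per birth year, the sampling error of a birth-year mean is so small that a departure of 1% of the mean exceeds it. An interval without any allowance could then show an effect on contacts, or on a secondary endpoint, where there is none.

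The extrapolation also costs precision even if the polynomial is exactly right. The power statements do not reflect this.

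**Working it through.** **The plan's own figure.** "We believe that a 5% change in the number of general practice contacts would" matter to workload; with an "average of 5 general practitioner contacts per 6-month period in the absence of" a named practitioner, 5% is 0.25 contacts. The spread is "a standard deviation of 6 contacts". For two means, n per group = 2(1.960 + 1.282)² × 36 / 0.25² ≈ 12,105; the t-based version gives 12,106, or 24,212 in total. The printed 24,212 per group therefore matches the two-group total. That is a separate matter and does not affect this point. What matters here is that the formula compares two simple means and contains no extrapolation to age 75.

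**Inputs**

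- SD 6 and effect 0.25 (Required sample size).
- Table 1 counts, assumed evenly spread: 105,250 / 5 = 21,050 per birth year below 75 and 84,931 / 5 ≈ 16,986 above. Table 1 calls its figures illustrative. The 10-year rows assume the same counts at ages outside the table.
- First-stage jump 80% − 5% = 0.75 (Table 1), treated as known. The target jump in the outcome is 0.25 × 0.75 = 0.1875.
- Ages at distance 1, 2, …, k from 75 on each side (k = 5 or 10), with 1939 dropped.
- τ, the SD of independent birth-year departures from the polynomial. **Not in the documents**; assumed 0.01 to 0.10 contacts (0.2% to 2% of the mean).

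**Formula.** Let S be the sum of squared weights that the fit gives to the birth-year means when predicting at age 75. For a line through 5 years, S = 1/5 + 3²/10 = 1.1 per side. Then

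- patient-level variance of the jump = S × (36/21,050 + 36/16,986);
- true variance = the same + 2Sτ².

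**Precision with no scatter (τ = 0)**

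| Years per side, fit | S | SE of jump | Power for 0.1875 | Residual birth-year df |
|---|---|---|---|---|
| 5, linear | 1.10 | 0.065 | 82% | 6 |
| 5, quadratic | 4.60 | 0.133 | 29% | 4 |
| 10, linear | 0.467 | 0.042 | 99% | 16 |
| 10, quadratic | 1.383 | 0.073 | 73% | 14 |

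A plain mean over 5 years would have S = 1/5 = 0.20. The linear extrapolation thus multiplies the variance by 1.10 / 0.20 = 5.5, and the quadratic by 4.60 / 0.20 = 23.

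**Effect of scatter, if patient-level errors are used**

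The sampling SE of one birth-year mean is 6/√21,050 = 0.041 below 75 and 6/√16,986 = 0.046 above.

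| τ (share of mean) | True SE / patient-level SE | Actual rate of a nominal 5% test | True SE, 5 years linear |
|---|---|---|---|
| 0.01 (0.2%) | 1.03 | 5.6% | 0.067 |
| 0.025 (0.5%) | 1.15 | 8.9% | 0.075 |
| 0.05 (1%) | 1.52 | 19.7% | 0.099 |
| 0.10 (2%) | 2.49 | 43.2% | 0.162 |

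Example at τ = 0.05: 1.1 × (36/21,050 + 36/16,986) = 0.00421; adding 2 × 1.1 × 0.0025 = 0.0055 gives 0.00971, whose square root is 0.099. The ratio is 0.099 / 0.065 ≈ 1.52. S multiplies both variance terms and cancels, so under independent scatter these rates are the same for every bandwidth and order.

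**An interval from birth-year means.** I simulated a t interval based on the residual scatter of the birth-year means. It rejects about 5% of the time under no effect at every τ tried. At 5 years linear its power is about 68% with no scatter and 36% at τ = 0.05.

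**The case against.** The strongest reply is that ordinary least squares names how the models are fitted, not how their errors are computed. It is compatible with clustered, cell-based or bootstrap errors, and a condensed article may leave that choice to the full protocol or analysis plan. This stands. A reader might infer that the plan treats all patients as independent information about the age trend; no sentence says so, and the false-positive rates above are conditional on that choice. The methods cited for rounded age are also not at hand, so they may carry an error treatment that the article does not describe.

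It also stands that τ is assumed and may be negligible. The placebo thresholds could expose scatter, although the article gives no rule for carrying what they show into the primary interval. The article further discloses dependence on specification and on bandwidth.

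The scatter model assumes independent departures. The article's own worry, a change of slope near the threshold, is smooth misspecification. For that, varying bandwidth and order does help, and a birth-year-means interval is not a full answer.

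The objection does not reach the power statements. These are positive claims, and they need qualifying whatever standard error is used.

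**Conclusion.** The point holds in a limited form. The article's stated handling of the rounded age covers the estimate and its robustness and gives no allowance in the confidence interval, while its precision claims mention patient numbers and, once, bandwidth. It is not shown that the planned intervals are wrong. If patient-level errors are used, the harm runs from trivial (about 6% at τ = 0.01) to serious (43% at τ = 0.10).

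The power result does not depend on τ. With the Table 1 counts and a 75-point first stage, only the 10-year linear fit exceeds the stated 90% (99%); the other three settings in the table give 82%, 73% and 29%. This assumes an SD of 6 and even, illustrative counts; the exclusions still to be applied would lower the power further.

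**What to change.** **Statistical methods**

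- State the standard-error method for the jump and the ratio.
- Beside the patient-level interval, report one based on the scatter of birth-year means around the fitted polynomials, with a t reference on the number of birth years minus fitted parameters. With 5 to 10 values per side, ordinary sandwich errors clustered on birth year are not a safe substitute.
- For each endpoint, report a lack-of-fit test of the polynomial against separate birth-year means at the chosen bandwidth and order.
- Where that test or the placebo thresholds show misfit, base the conclusion on the birth-year-means interval. The test has few degrees of freedom, so report both intervals whatever its result.

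I would not make the wider of the two intervals the primary one. With no scatter that rule rejects only about 2.5% of the time at 5 years linear.

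**Required sample size; Strengths and limitations**

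Say that power for a 5% change depends on bandwidth, polynomial order, polynomial fit and the 75-point first stage, not on patient numbers alone, and give figures for the settings likely to be used.

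**Cost.** A few sentences and a few lines of code on data already to be held. The price is a wider interval (power about 68% instead of 82% at 5 years linear with no scatter) and a less favourable power statement.
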